### Statistical Methods and Analysis

#### Sample Size

The sample size is estimated using the sample size formula for estimating proportion between two groups**.** Considering the reported fall incidence with FRIDs as 73% [12], the sample size is estimated to be 478 (each arm: 239), with 90% power (as the outcomes measures are only falls and do not include any mortality, we have set the power to 90%) and 5% level of significance to detect a minimum of 20% reduction in falls in the intervention group relative to the control group (relative risk reduction of 20%). Considering the dropout of 10%, the final sample size will be 526 (263 in each arm). A total of135 participants are expected to be recruited from each center.

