#### Incremental Cost-Effectiveness Ratio (ICER)

Incremental Cost-Effectiveness Ratio (ICER) will be calculated by dividing the difference in costs between the interventions by the difference in outcomes. The ICER represents the additional cost per unit of outcome achieved by one intervention compared to another.

We will be following the intention-to-treat strategy to analyze the data. Therefore, even participants who discontinue but have at least 1 follow-up will be included in the study to achieve the required sample size, taking into account their age and health status.

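### The 10% dropout allowance is added to 478 (giving 526) instead of being divided out (532), so 526 covers a loss of only 9.1%; a minor correction

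*Protocol article*

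**What the plan says.** The Sample Size section gives these inputs, in order:

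- Control rate: "Considering the reported fall incidence with FRIDs as 73" per cent.
- Effect: a "relative risk reduction of 20" per cent.
- Error rates: "we have set the power to 90" per cent, and a "5% level of significance to detect a minimum of 20% reduction in falls". Whether the test is one- or two-sided is not stated.
- Calculated need: "the sample size is estimated to be 478 (each arm: 239").
- Final size: "Considering the dropout of 10%, the final sample size will be 526 (263 in each arm").
- Centre target: 135 "participants are expected to be recruited from each center". The number of centres is not given. Study Design and Setting says only that the trial is multicentre.

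The second paragraph under Incremental Cost-Effectiveness Ratio (ICER) sets the analysis population. It follows intention to treat and says that "even participants who discontinue but have at least 1 follow-up will be included in the study to achieve the required sample size".

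**The concern.** The section links three figures: a required number, a dropout rate and an enrolment target. A reader will take them to mean that enrolling 526 and losing 10% leaves the 478 on which the 90% power rests. It does not, because the allowance was computed as a share of the number required, whereas dropout is lost from the number enrolled.

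At stake is whether the stated target is correct. The final size is the figure against which recruitment will be judged and reported. A trial that enrols exactly 526 and loses exactly 10% to analysis will have met its enrolment target and kept within its dropout allowance, yet will fall short of its own stated requirement.

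**Working it through.** **Inputs (all from the Sample Size section).** Required number N = 478, or n = 239 per arm; dropout d = 0.10; stated final size 526, or 263 per arm; control proportion 0.73; relative reduction 20%, so the intervention proportion is 0.73 × 0.80 = 0.584; power 90%; significance level 5%, taken as two-sided (assumption).

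**1. Reproduce the plan's final size.**
- N × (1 + d) = 478 × 1.10 = 525.8, rounded up to 526.
- Per arm: 239 × 1.10 = 262.9, rounded up to 263.

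Both match exactly, so this is how 526 was obtained.

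**2. Final size that retains 478 after a 10% loss.**
- N / (1 − d) = 478 / 0.90 = 531.1.
- Per arm: 239 / 0.90 = 265.6, rounded up to 266, so 532 in total.
- Check: 532 × 0.90 = 478.8, which meets 478.
- Difference from the plan: 532 − 526 = 6 participants, 3 per arm.

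**3. What 526 delivers.**
- After a 10% loss: 526 × 0.90 = 473.4, about 473 (236.7 per arm). Shortfall: 478 − 473.4 = 4.6, about 5.
- Largest loss that still leaves 478: 1 − 478/526 = 48/526 = 9.1%.

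**4. Effect on power.** Two-proportion normal approximation, pooled variance under the null, no continuity correction, independent participants.

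| Evaluable per arm | 0.73 vs 0.584 | 0.73 vs 0.59 |
|---|---|---|
| 239 | 92.2% | 90.1% |
| 236 | 91.9% | 89.7% |

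The second column uses the stated effect. The third is a sensitivity check. With 0.584 the formula needs 221 per arm (442 in total), or 234 per arm (468) with continuity correction. With the intervention rate rounded to 0.59 it gives exactly 239 per arm. The article does not say that this rounding was made, so it is an inference. The change in power is about 0.3 points at the stated rates and about 0.4 at the rounded one.

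**5. Centre target.** 526/135 = 3.9. If there are four centres (assumption), 4 × 135 = 540 enrolled and 540 × 0.90 = 486 evaluable, which exceeds 478.

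**The case against.** Four points can be made for the plan.

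*The denominator of the 10% is not stated.* If it means an allowance added to the calculated size, 478 plus 10% is 526 and nothing conflicts. This explains the figure, but nothing in the article defines the 10% in that way, and dropout is ordinarily a share of those enrolled. It does mean that the three figures conflict only on that ordinary reading.

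*Dropping out is not the same as being lost to analysis.* The intention-to-treat paragraph keeps discontinuers who have at least one follow-up, and The Follow-Up Phase schedules monthly calls and three-monthly visits. Many who leave would therefore still count, and a non-evaluable loss of 9.1% or less would leave 478. This stands: 473 is what remains if the full 10% are lost to analysis, and is not a forecast. It does not alter the inflation arithmetic.

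*The gap has no practical effect.* At the stated rates, 473 exceeds both 442 and 468, and power stays above 90%. This also stands. A reader might infer from a shortfall against the required number that the trial is underpowered, and the figures do not support that. Even on the inferred 0.59 rate, power is 89.7%, a few tenths of a point below the target.

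*The centre target is not a second total.* A reader might infer that the section gives two conflicting enrolment totals, 526 and 540. It does not. It gives one total and an expected number per centre, and 540 appears only if four centres are assumed. On that assumption 526/4 = 131.5, and 135 may simply be a rounded-up target. The four in Sampling Technique counts departments, not centres.

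**Conclusion.** The point holds as a minor correction of a stated figure. With 10% read as the share of enrolled participants lost to analysis, 526 leaves about 473, roughly 5 (1.0%) below the stated 478. The enrolment that matches the stated allowance is 532, which is 6 more than planned.

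The arithmetic is certain on that reading. The size of any real shortfall is not, because the rule on discontinuers may hold the evaluable loss below 10%, and because recruitment may exceed 526 if there are four centres of 135. The power figures further assume a two-sided test and independent participants; they concern the dropout step only and do not address whether the size is otherwise adequate.

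**What to change.** Change one sentence in the Sample Size section, in either of two ways:

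- keep 526 (263 per arm) and state that it allows for 9.1% of enrolled participants being non-evaluable, meaning not retained under the article's own rule of at least one follow-up; or
- keep the 10% allowance and restate the final size as 532 (266 per arm).

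In the same edit, state the number of centres so that 135 per centre can be read against the total.

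The first option costs only the wording. The second adds 6 participants on paper, and none in practice if there are four centres recruiting 135 each.

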#### Data Analysis

The data will be entered in Research Electronic Data Capture (REDCap) and will be analyzed using Stata (version 16; StataCorp) software. Data will be stored in a secure server or cloud-based platform. A principal investigator and a co–principal investigator will have access to the REDcap data. The statistician will be given access to the blinded REDcap data. The occurrence of falls and fall risk during the study period will be summarized as frequency and percentages. The number of falls at these time points will be reported using the median (IQR) values. The fall risk score will be reported as mean (SD) or median (IQR) based on the normality of the data. The Mann-Whitney *U* test and Friedman test (chi-square test) will be used to analyze the change in the frequency of falls (%) at each time point between the groups and within the groups, respectively. The chi-square test will be used to analyze the fall risk score category at each time point between the groups. Additionally, repeated measures ANOVA (or Friedman test) and unpaired *t* test (or Mann-Whitney *U* test) will be used to assess the within-group fall risk score at different time points and at each time point within the group, respectively. Poisson regression analysis (both bivariate and multivariate) will be conducted to explore the association between the dependent variable (ie, the number of falls and fall risks assessed using Timed Up and Go and the Performance-Oriented Mobility Assessment) and independent factors (eg, age, gender, education, chronic illness, and intervention category). Adjusted risk ratios with 95% CIs will be reported for the factors included in the multivariate Poisson regression model. The rationality of prescriptions will be summarized using frequencies and percentages. Subgroup analysis will be performed for participants with recurrent fall history and different age categories.

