#### Baseline Assessment

Demographic details, such as age, gender, occupation, education, BMI, disease conditions details, and list of drugs used (including FRIDs with their costs and orthostatic hypotension details) will be collected from all the participants. Drug details, such as the name of the drug, indication, frequency, route of administration, and duration of use will also be collected. The rationality of the prescriptions will be assessed by the World health Organization prescription indicators.

Participants will then be asked about their previous fall history using the fall history questionnaire of McCrum 2020 [8] and their concern for falls assessed by the Fall Efficacy Scale [9,10]. Quality of life will be assessed by administering the EQ-5D-5 L questionnaire. Once the baseline data collection is completed, they will be assessed for fall risk. The fall risk assessment will be conducted by a staff nurse using the Timed Up and Go test and the Tinetti Performance-Oriented Mobility Assessment Tool.

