### The Follow-Up Phase

Each participant will be followed for a period of 1 year after their enrollment into the study. Both groups will be followed up for 1 year. Each participant will be given a diary to record the falls and other adverse events. They will be followed up monthly over the phone for falls and for occurrence of other adverse events and for improving adherence to the intervention protocols of the study. Every 3 months, they will be followed up physically to assess fall risk, inquire about any fall history, and note any adverse events during that period.

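### The rank tests on falls analyse a change with no stated reference; compare falls in equal follow-up windows instead, and use fall history as a covariate

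*Protocol article*

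**What the plan says.** All references are to the protocol article.

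- **Data Analysis.** The Mann-Whitney and Friedman tests "will be used to analyze the change in the frequency of falls (%) at each time point between the groups and within the groups, respectively". No reference value for the change is given. The same section reports the occurrence of falls and fits a Poisson regression to the number of falls, with "independent factors (eg, age, gender, education, chronic illness, and intervention category" as explanatory variables.
- **Baseline Assessment.** "Participants will then be asked about their previous fall history using the fall history questionnaire". The look-back period is not stated.
- **The Follow-Up Phase.** Falls are captured by diary and monthly calls for a year, and at visits: "Every 3 months, they will be followed up physically to assess fall risk, inquire about any fall history, and note any adverse events during that" (the quote stops one word before the sentence ends).
- **Abstract, Results.** Efficacy is fall frequency; the word for change is attached only to the fall risk scores.
- **Sample Size.** "Considering the reported fall incidence with FRIDs as 73"%, the trial is sized "to detect a minimum of 20% reduction in falls in the intervention group relative to the control group", which is a comparison of two proportions with no change score.

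**The concern.** The rank tests are the only between-group tests named for falls apart from the Poisson model, which is described as exploring associations. The quantity they test is a change, and a reader cannot tell from what. Two literal readings are possible, and each causes a problem.

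1. **Change from baseline.** The only fall value before follow-up is a recalled history. A count over one window would be set against a count over another, possibly longer, window. A patient with a constant fall rate would then appear to improve, and the noise of the baseline count would enter the between-group test.
2. **Change between successive follow-up visits.** If the intervention lowers the fall rate and keeps it lower, the change from one quarter to the next averages zero in both arms, so the test has nothing to detect. The first visit also has no earlier follow-up value.

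The baseline fall history is already collected. As a covariate it could sharpen the treatment estimate, but it is not among the factors named for the Poisson model.

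**Working it through.** **The plan's own figure.** Inputs from Sample Size: control 0.73; intervention 0.73 × 0.80 = 0.584; "5% level of significance" (taken as two-sided); 90% power. The pooled two-proportion formula gives 221 per arm, and 234 with continuity correction. The article states "the sample size is estimated to be 478 (each arm: 239"), about 2% above 234. Then 478 × 1.10 = 525.8, rounded to 526. Power at 239 per arm is 92.2%. None of this depends on a change score.

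**Assumptions for the rest.** The 73% is taken as a 12-month figure (the article gives no period). Rates are constant over time, patients are independent, the follow-up window is 3 months, and the look-back is 3, 6 or 12 months. Falls are Poisson, or gamma-Poisson with frailty variance k. The annual mean is μ = −ln(1 − p) for Poisson and μ = [(1 − p)^(−k) − 1]/k otherwise:

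| k | control μ | intervention μ | rate ratio |
|---|---|---|---|
| about 0 | 1.31 | 0.88 | 0.67 |
| 0.5 | 1.85 | 1.10 | 0.60 |
| 1 | 2.70 | 1.40 | 0.52 |

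**Within groups, no effect.** For Poisson falls, the share of controls with at least one fall is 1 − 0.27^(L/12) over L months: 28% for 3 months, 48% for 6 and 73% for 12. A change from baseline to any quarter would therefore read as a drop of 20 points (6-month look-back) or 45 points (12-month), and zero if the windows match. The mean change in counts is −μ(L − 3)/12; at k = 1 this is 0.0, −0.7 and −2.0 falls for L = 3, 6 and 12. In simulation, a Friedman test that includes the baseline value rejects in 100% of runs at 6 or 12 months, and close to the nominal 5% at 3 months.

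**Between groups, no effect.** Both arms share the same windows, so the artefact cancels. Simulated type I error for the test of change is 5.1% to 6.1% (k = 1, 2,000 runs).

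**Between groups, planned effect.** The variance of a change is V(B) + V(F) − 2·Cov(B, F), where B is the baseline and F the follow-up count. For pure Poisson counts the covariance is zero, so the ratio to V(F) is (L + 3)/3: 2, 3 and 5 for L = 3, 6 and 12. With equal variances the ratio is 2(1 − ρ), so change is noisier than the follow-up count only when the correlation ρ is below 0.5. Simulated Mann-Whitney power at 239 per arm for one 3-month window:

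| Quantity tested | k about 0 | k = 0.5 | k = 1 |
|---|---|---|---|
| Follow-up count | 56% | 83% | 95% |
| Change from 12-month recall | 17% | 22% | 24% |
| Change from 3-month recall | 32% | 59% | 88% |
| Change between successive quarters | about 5% | about 5% | about 5% |

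Repeat runs agree to within a few percentage points. With a 12-month follow-up window and a 12-month recall, count against change is over 99% against 85% (k about 0) and 99.7% against 98.8% (k = 0.5), with no loss at k = 1 or 2.

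**Fall history as covariate.** Adding log(1 + baseline falls), 12-month look-back, to the annual-count model changes the standard error of the log rate ratio from 0.101 to 0.091 at k = 0.5 (1 − 0.091/0.101 = 10% lower) and from 0.113 to 0.082 at k = 1 (27% lower). With no frailty, past falls carry no information and there is no gain.

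**The case against.** The strongest reply is that change here is loose wording. The preceding sentences summarise falls during the study and at the time points, and a Friedman test takes repeated values rather than differences. The abstract reserves change for the risk scores. On that reading the plan already compares falls at each visit between the arms and across visits within them. The reading is plausible, and if it is right the rewording costs nothing. It is not what the sentence says, however, and the two literal readings both do harm.

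Other parts of the reply stand in full:

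- A reader might infer that the fall history covers a different window from the follow-up. The article gives no look-back, so the mismatch is only a possibility.
- A reader might infer that the randomised comparison is biased. It is not: the window artefact cancels between arms.
- A reader might infer that most of the power is always lost. That holds for a long recall against a short follow-up window. It does not hold for equal 12-month windows with correlated counts, and at matched 3-month windows the loss is modest when k = 1.
- The Poisson model on the number of falls uses no change score, so the trial is not left without a usable analysis.
- The covariate list is given as examples. Fall history is not excluded, and recurrent fall history already defines a subgroup. Naming it is an improvement, not the correction of an error.

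**Conclusion.** The point holds in a limited form. The article fixes a change in fall frequency as the tested quantity without a reference, and this does not fit its own efficacy measure or sample size basis. If the reference is recalled history, within-group results are uninterpretable unless the look-back equals the follow-up interval. The between-group test keeps its type I error, but its power at one 3-month visit may fall from about 56–95% to 17–24% (12-month recall) or 32–88% (3-month recall). If the reference is the previous quarter, power against a constant effect is about 5%. These figures rest on assumed fall distributions, an assumed annual 73%, an assumed look-back, constant rates and independent patients. The documents do not show which reading is intended.

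**What to change.** In Data Analysis:

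1. Replace the change in fall frequency by the falls recorded in follow-up windows of equal length, compared between the groups.
2. Keep the recalled baseline history out of the Friedman series, so that it contains follow-up windows only.
3. Name baseline fall history (number of falls in the look-back, with that period stated) among the covariates of the multivariate Poisson model for the number of falls.

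The cost is a change of wording. The data are already to be collected and the 239 per arm is unaffected. The only loss is a descriptive within-group change from baseline.

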**Results:**

The study received a grant from the Indian Council of Medical Research–Safe and Rational Use of Medicine in October 2023. The study is scheduled to commence in April 2024 and conclude by 2026. Efficacy will be measured by fall frequency and changes in fall risk scores. Cost-effectiveness analysis will also include the incremental cost-effectiveness ratio calculation. Adverse events related to deprescription will be recorded.

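### The sample size rests on one comparison of the proportion of patients who fall, but the analysis section tests falls visit by visit and does not say which measure or time point decides the trial

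*Protocol article*

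**What the plan says.** All references are to the protocol article.

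- **Sample Size.** "The sample size is estimated using the sample size formula for estimating proportion between two groups". The inputs are a 73% fall incidence and a 20% relative reduction, at 90% power and 5% significance, with the aim "to detect a minimum of 20% reduction in falls in the intervention group relative to the control group". The result is 478 participants (239 per arm), raised to 526 for dropout. No time window is attached to the 73%.
- **Data Analysis, description.** "The occurrence of falls and fall risk during the study period will be summarized as frequency and percentages". For counts, "The number of falls at these time points will be reported using the median (IQR) values".
- **Data Analysis, tests of falls.** The Mann-Whitney and Friedman tests "will be used to analyze the change in the frequency of falls (%) at each time point between the groups and within the groups", in that order. Mann-Whitney is thus the between-group test, and Friedman, with chi-square in brackets, the within-group test. The separate between-group chi-square test is for the fall risk score category.
- **Data Analysis, regression.** Bivariate and multivariate Poisson regression is planned to explore associations. The dependent variables are the number of falls and the fall risks from Timed Up and Go (TUG) and the Performance-Oriented Mobility Assessment (POMA). Intervention category is one of several listed factors, and adjusted risk ratios with 95% CIs are promised.
- **Abstract, Results.** "Efficacy will be measured by fall frequency and changes in fall risk scores". Neither measure is ranked above the other.

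**The concern.** The sample size calculation fixes a hypothesis: the proportion of participants who fall differs between arms. The analysis section sets out its tests in some detail, yet none is a single comparison of that proportion over the whole study. Falls are tested between groups at every time point, and fall risk scores are tested at every time point too.

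Two things are at stake. First, the 90% power belongs to a test that is not stated, and the stated tests may have more or less. Second, with several measures and several visits unranked in an open-label trial, a favourable conclusion could rest on whichever visit or score happens to be significant. A smaller matter is the planned summary: a median count over a short interval may be unable to show the effect the trial was sized to detect.

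**Working it through.** **1. Reproduce the plan's figure.** Inputs from Sample Size: p1 = 0.73; p2 = 0.73 × 0.80 = 0.584; difference d = 0.146; mean p̄ = 0.657; power 90% (z = 1.2816); two-sided 5% (z = 1.96). Sidedness is not stated.

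- n = [1.96·√(2·0.657·0.343) + 1.2816·√(0.73·0.27 + 0.584·0.416)]² / 0.146² = 220.1, so 221 per arm.
- With continuity correction: (220.1/4)·[1 + √(1 + 4/(220.1·0.146))]² = 233.6, so 234 per arm (468 in total).

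The stated 239 per arm is close: 234 is 2.1% below it. One-sided versions give 180 or 193 per arm, and an absolute 20-point reduction gives 121 or 131, so those readings do not fit. The powered quantity is one two-sided comparison of the proportion who fall.

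**2. Power of that single test at 239 per arm** (no continuity correction, no clustering):

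Φ{[0.146·√239 − 1.96·√(2·0.657·0.343)] / √(0.73·0.27 + 0.584·0.416)} = Φ(1.42) = 92.2%.

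**3. Power in one quarter.** The assumptions are that 73% and 58.4% are 12-month figures, that time points are separate quarters (four physical visits, every 3 months), and that risk is constant.

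- Without overdispersion: 1 − 0.27^(1/4) = 27.9% and 1 − 0.416^(1/4) = 19.7%.
- With gamma-distributed individual rates (negative binomial counts), the yearly mean is set so that the 12-month proportions stay at 73% and 58.4%.

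| Assumed dispersion | Fallers per quarter | Power, any fall in one quarter | Simulated power, rank test on quarterly counts | Quarterly medians | 12-month medians |
|---|---|---|---|---|---|
| 0 (Poisson) | 27.9% vs 19.7% | 56% | about 60% | 0 vs 0 | 1 vs 1 |
| 0.5 | 34.0% vs 22.7% | 78% | about 84% | 0 vs 0 | 1 vs 1 |
| 1 | 40.3% vs 26.0% | 92% | about 96% | 0 vs 0 | 2 vs 1 |

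The quarterly median is 0 wherever fewer than half of an arm fall in the quarter, which holds in every row.

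**4. Repeated testing.** Four independent tests at 5%: 1 − 0.95⁴ = 18.5%. Simulated Mann-Whitney tests on four sets of quarterly counts with no true effect gave 17.3% to 17.6%. Twelve independent tests (falls, TUG and POMA at four visits, or falls at 12 monthly contacts): 1 − 0.95¹² = 46.0%. These are upper figures, because correlated tests give less.

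**The case against.** Several stronger conclusions are tempting, and the document does not support them.

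- **That the intervention effect on falls is never tested outside the visits.** The Poisson regression includes intervention category, is not tied to a visit and promises adjusted risk ratios with CIs. It narrows the gap without closing it: its outcome is the number of falls, not whether a participant fell, and it is worded as exploratory.
- **That a rank test of a percentage is undefined.** If each participant is coded as fell or did not fall, the Mann-Whitney test is in effect a comparison of proportions. For 174/239 against 140/239 it gives p = 0.00107, against 0.00105 for the uncorrected chi-square test. What remains is that it is repeated at each time point.
- **That power falls to 56%.** This is the worst of the cases checked. The section does not say whether falls at a time point are counted per interval or cumulatively. If cumulatively, the month-12 test covers the full follow-up year, although nothing marks it as the deciding one.
- **That the reported medians must be the same in both arms.** This held for quarterly counts in the scenarios checked. Over 12 months, at dispersion 1, the medians are 2 and 1.
- **That the false-positive risk is 18.5% or 46%.** Both figures assume independent tests. Cumulative counts, or correlated TUG and POMA scores, would lower them.

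It is also fair to say that a condensed article may leave the naming of a primary analysis and multiplicity control to the full protocol or analysis plan, and that Sample Size does identify falls as the outcome. The point therefore does not rest on missing detail. It rests on two adjacent sections that do state their methods, and state different ones.

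**Conclusion.** The point holds as a mismatch between the powered comparison and the stated analyses. The trial is sized on one test of the proportion who fall. The analysis section describes that proportion over the study without testing it once, tests falls at each time point, and models the number of falls in an exploratory regression. No fall measure, fall-risk measure or time point is stated to decide the trial.

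The size depends on how time points are defined and how falls are distributed, and the document gives neither. For any fall in one separate quarter, power runs from about 56% (constant risk, no overdispersion) to about 92% (dispersion 1), against 92.2% for the single 12-month comparison by the same formula. All of these ignore clustering by physician. The false-positive risk over four quarterly tests is up to about 18.5%. The firm conclusion is that the stated 90% does not automatically apply to the stated tests, not that power is necessarily lost. The sample size arithmetic is not at fault on this point.

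**What to change.** State one primary analysis in Data Analysis and have Sample Size refer to it:

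- **Outcome:** the proportion of participants with at least one fall over 12 months.
- **Test:** once, at two-sided 5%.
- **Estimate:** a risk ratio with 95% CI from a log-link model (for example modified Poisson) that accounts for the randomized physician and the seniority stratum. Adjustment for baseline fall history is optional.
- **Secondary:** number of falls, TUG, POMA and all per-visit comparisons. Say whether falls at a visit are counted per interval or cumulatively.
- **Summaries:** report fall rates per person-year alongside the medians.

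The cost is wording only. Diaries, monthly calls and 3-monthly visits already capture any fall over the year, and physician and stratum are known from randomization. The change should be made before outcome data by arm are seen.

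### The chi-square test of fall-risk category cannot use the baseline category and, if there are three or more levels, also ignores their order

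*Protocol article*

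**What the plan says.** The Data Analysis section of the protocol article names the test: "The chi-square test will be used to analyze the fall risk score category at each time point between the groups". It names no trend, rank or ordinal method for the category and no adjustment for baseline.

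Three other places bear on the point:

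- Abstract, Results: "Efficacy will be measured by fall frequency and changes in fall risk scores".
- Baseline Assessment: "The fall risk assessment will be conducted by a staff nurse using the Timed Up and Go test", together with the Tinetti mobility assessment. The Follow-Up Phase section repeats the fall-risk assessment every 3 months for a year, so each follow-up category has a baseline counterpart.
- Data Analysis again: fall risk is summarized as frequencies and percentages. A Poisson regression takes falls and fall risk as dependent variables, has intervention category among its example factors, and reports adjusted risk ratios with 95% CIs.

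The article does not give the number of fall-risk categories or their cut-points.

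**The concern.** Fall-risk categories run from lower to higher risk. With three or more levels, a Pearson chi-square test treats them as interchangeable labels and spreads its power over every pattern of difference, including patterns that are neither benefit nor harm. If the intervention shifts patients steadily towards lower risk, a test that uses the order is more likely to detect it.

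The second loss does not depend on the number of levels. A patient's category at follow-up is likely to be related to the category at entry. A two-way table of arm by follow-up category has no place for that information, so its prognostic value is discarded although the data are collected anyway.

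Finally, the test yields a p value but no estimate with an interval. At stake is the sensitivity and readability of one analysis of fall risk, which the article counts as an efficacy measure alongside fall frequency.

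**Working it through.** **1. The plan's own figure.** The article sizes the trial on falls: "Considering the reported fall incidence with FRIDs as 73" per cent, "relative risk reduction of 20" per cent, 90% power, "5% level of significance" (two-sided assumed, as the article does not say). The intervention rate is then 0.73 × 0.80 = 0.584, the difference 0.146 and the mean rate 0.657.

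- Uncorrected: n = [1.960 × √(2 × 0.657 × 0.343) + 1.282 × √(0.73 × 0.27 + 0.584 × 0.416)]² / 0.146² ≈ 220.1, so 221 per arm.
- With continuity correction: (220.1/4) × [1 + √(1 + 4/(220.1 × 0.146))]² ≈ 233.6, so 234 per arm.
- Stated: "the sample size is estimated to be 478 (each arm: 239"). The difference is 5/239 = 2.1%, so the figure is reproduced closely enough.
- Dropout: 478 × 1.10 = 525.8, matching "Considering the dropout of 10%, the final sample size will be 526 (263 in each arm").

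No power is stated for fall-risk category. What follows takes 239 per arm as the evaluable number.

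**2. Assumptions.** The article supplies none of these: a normal latent risk score with a shift of 0.25 SD, cut into equal-sized control-arm categories; a baseline correlation of 0.5 to 0.7; two-sided 5%; patients treated as independent.

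**3. Loss from ignoring order.** For n per arm the chi-square noncentrality is λ = n × Σ(p₀ − p₁)²/(p₀ + p₁), on k − 1 degrees of freedom for k levels. A rank or trend test spends nearly all of λ on one degree of freedom when the shift is steady.

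- Three levels. Control 0.333/0.333/0.333, intervention 0.428/0.324/0.248. λ = 239 × 0.0245 = 5.86. Chi-square (2 df): 57%. One-df test: √5.86 = 2.42, and Φ(2.42 − 1.96) = 68%. Loss about 10 points.
- Four levels. Control 0.25 each, intervention 0.336/0.263/0.224/0.178. λ = 6.35. Chi-square (3 df): 54%. Rank test: z = 2.51, power 71%. Loss about 17 points.
- Two levels. Both tests have 1 df, so the loss is zero.

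The loss varies with the effect. Where the one-df test has 80% power, chi-square has 70.9% with three levels and 64.5% with four, losses of 9.1 and 15.5 points. With common odds ratios from 1.2 to 2.0 at 239 per arm, the loss runs from 2.1 to 10.5 points with three levels and from 3.4 to 17.0 with four.

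**4. Loss from ignoring baseline, two even levels.**

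- Unadjusted: 0.500 against Φ(0.25) = 0.599; z = 0.0987/√(2 × 0.549 × 0.451/239) = 2.17; power 58%.
- A latent correlation ρ gives a correlation between the two binary variables of φ = (2/π) × arcsin ρ: 0.333 for ρ = 0.5 and 0.494 for ρ = 0.7.
- Adjusted z = 2.17/√(1 − φ²) = 2.30 and 2.49; power 63% and 70%. The gain is 5 to 12 points.

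**5. Simulation under the same assumptions.**

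| Levels (equal) | Chi-square | Rank test | Category score adjusted for baseline category |
|---|---|---|---|
| 2 | 56–58% | same | 60–70% |
| 3 | 56–58% | 67–68% | 76–85% |
| 4 | 52–55% | 70–71% | 78–91% |

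The last column is a linear comparison of category scores, not a fitted proportional-odds model, so it shows only roughly what the recommended model would achieve.

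**6. A case that goes the other way.** With 30/40/30 against 30/50/20 at 239 per arm, only the boundary between the upper two categories moves. λ = 239 × (0.01/0.9 + 0.01/0.5) = 7.44, so chi-square has 68% power; a rank test has 30%.

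**The case against.** The case for leaving the plan alone has four parts.

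- **The number of levels is not given.** An article may leave it to a fuller document, and with two levels order does not matter. This stands: a reader might infer a fixed loss of 8 to 17 points, but the documents do not support that, because the figure presupposes three or four levels and a particular effect. The baseline loss does not depend on this.
- **The rest of the section covers part of the gap.** A reader might infer that the plan gives no direction or effect size for fall risk, or no other between-group comparison. Neither follows. Percentages by group show direction, and the Poisson model includes intervention category and reports risk ratios with intervals. But that model is described as exploring associations, does not name baseline fall risk among its example factors, and leaves open whether score or category is modelled. For an ordered category of three or more levels a risk ratio also needs a dichotomy that the article does not state. The unpaired test of the score is worded as within the group; that may be a slip, but as written it does not fill the gap.
- **The category is a secondary view.** The abstract speaks of changes in scores, not categories, and the trial is sized on falls. This stands and limits the weight of the point.
- **The calculations treat patients as independent, yet the Randomization section randomizes physicians.** This stands. The absolute powers do not describe this trial, and a model with only arm and baseline category could give too narrow an interval if outcomes correlate within physician.

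**Conclusion.** The point holds as one of efficiency and reporting, not as an error: the chi-square test is a recognized choice for comparing categories, but it discards information that the trial collects. Ignoring the baseline category costs about 4 to 12 points of power even with two levels. Ignoring order costs about 10 points with three levels, about 15 or more with four, and nothing with two.

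These sizes rest on 239 per arm, a latent shift of 0.25 SD, a baseline correlation of 0.5 to 0.7, roughly even categories and independent patients. Only the first comes from the article. The advantage of an ordered test also assumes a shift in one direction across the categories.

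A reader might infer that the trial as a whole is underpowered. The documents do not support that on this ground, since the stated 90% power concerns falls and is unaffected.

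**What to change.** In Data Analysis, replace the chi-square test of fall-risk category with ordinal logistic regression at each time point (ordinary logistic regression if the category is binary), with arm and baseline category as terms and standard errors that allow for clustering by randomized physician. Report the odds ratio with its 95% CI. State the number of levels and the cut-points for each tool in the same place.

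The cost is a sentence or two and a standard Stata command, with no new data apart from a physician identifier in the analysis file. The small downside is that proportional odds must be checked: if the effect is confined to one category boundary, an ordered test can have less power than chi-square. Showing the category percentages by arm beside the odds ratio would make such a pattern visible.
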